## Abstract

**Background:**

Nodding syndrome (NS) is a devastating epileptic illness of unknown aetiology mainly affecting children 5–15 years of age. Head nodding distinguishes NS from other forms of epilepsy. Other manifestations of the illness include mental and physical growth retardation. Many children die as a result of falling in fires or drowning. Recently, it was shown that NS is only one of the phenotypic presentations of onchocerciasis associated epilepsy (OAE). Despite the strong epidemiological association between epilepsy and onchocerciasis, the causal mechanism is unknown. After implementation of bi-annual community directed treatment with ivermectin (CDTi) and larviciding of rivers in northern Uganda, new cases of NS have ceased, while new cases continue to emerge in South Sudanese onchocerciasis-endemic areas with an interrupted CDTi programme. This study is designed to evaluate the potential effects of bi-annual CDTi on reducing the incidence of NS/OAE in onchocerciasis-endemic areas in South Sudan.

**Methods:**

A pre-intervention door-to-door population-based household survey will be conducted in selected onchocerciasis-endemic villages in Mundri and Maridi Counties, which have a high prevalence of epilepsy. Using a validated questionnaire, the entire village will be screened by community research assistants for suspected epilepsy cases. Suspected cases will be interviewed and examined by a trained clinical officer or medical doctor who will confirm or reject the diagnosis of epilepsy. Bi-annual CDTi will be implemented in the villages and a surveillance system for epilepsy set up. By implementing an epilepsy onchocerciasis awareness campaign we expect to obtain > 90% CDTi coverage of eligible individuals. The door-to-door survey will be repeated two years after the baseline survey. The incidence of NS/OAE will be compared before and after bi-annual CDTi.

**Discussion:**

Our study is the first population-based study to evaluate the effect of bi-annual CDTi to reduce the incidence of NS/OAE. If the study demonstrates such a reduction, these findings are expected to motivate communities in onchocerciasis-endemic regions to participate in CDTi, and will encourage policy makers, funders and other stakeholders to increase their efforts to eliminate onchocerciasis.

**Electronic supplementary material:**

The online version of this article (10.1186/s40249-018-0496-2) contains supplementary material, which is available to authorized users.

## Multilingual abstract

Please see Additional file 1 for translations of the abstract into the five official working languages of the United Nations.

## Background

Nodding syndrome (NS) is a debilitating neurological condition, characterized by multiple seizure types with head nodding being predominant [1]. Head nodding manifests as spontaneous head drops towards the chest because of atonic seizures. Advanced cases of NS usually present with mental and physical growth retardation, along with other neurological abnormalities including psychiatric manifestations [2, 3]. The disease mainly develops in children 5–15 years of age [1, 4].

Initial cases of a condition consistent with NS were reported in Tanzania in the early 1960s [5], followed by South Sudan in the 1990s and 2001 [6, 7] and in northern Uganda in 2007 [4].

Several studies suggested an association of NS and other forms of epilepsy with onchocerciasis [1, 4, 8, 9]. Recently it was shown that NS is only one of the phenotypic presentations of onchocerciasis-associated epilepsy (OAE), which may include absences, atonic and myoclonic neck seizures, and Nakalanga features (growth retardation) [10]. It remains, however, unclear how onchocerciasis might cause epilepsy because so far the parasite has never been observed in the brain [9]. An auto-immune phenomenon triggered by the *Onchocerca volvulus* has been proposed as a possible explanation [11].

### Burden of NS/OAE in South Sudan

Since the first cases of NS were reported from the Western Equatoria region of South Sudan in the 1990s, the region has continued to have a high rate of new NS cases and other forms of epilepsy. In 2001, the World Health Organization (WHO) estimated the prevalence of NS to be at 4.6% among a small population in Western Equatoria, which is considered to have the highest burden of the disease [4]. During a small household survey conducted in 2013 in the same area (Mvolo), one in six children had epilepsy (NS and other forms of epilepsy), one in two households had at least one child with epilepsy, and one in three households had at least two children with epilepsy [12]. The South Sudan Relief and Rehabilitation Commission reported an epilepsy prevalence of 8.4% (including NS and other forms of epilepsy), consistent with the 2013 household survey [13].

As part of an initiation visit for a study on NS in Lui, Mundri East (June 2016), we conducted house-to-house interviews in communities living around Lui hospital. We randomly selected households and detected cases of NS and other forms of epilepsy in about half the households, with some households having more than one person with epilepsy, as was observed in Mvolo.

### Onchocerciasis in South Sudan

South Sudan is amongst the highly endemic countries for onchocerciasis in Africa, with the disease being endemic in around half (49%) of the country [14]. The most highly endemic foci of onchocerciasis in South Sudan are in Western Equatoria, and the Northern and Western Bahr el Ghazal areas (Fig. 1).

**Fig. 1 Fig1:**
[figure not shown]
South Sudan community directed treatment with ivermectin (CDTi) areas and distribution of onchocerciasis [15]

In 2008, more than 80% of individuals in some villages in Western Equatoria, and the Northern and Western Bahr el Ghazal areas had palpable onchocerciasis nodules and the prevalence of river blindness was more than 12% [15]. In 2006, around 40% (4.1 million) of South Sudan’s population were at risk of onchocerciasis, of which 3.6 million were eligible for CDTi [15]. However, only 26% of the eligible population received treatment with ivermectin in the five CDTi project areas [15] (Table 1).

**Table 1 Tab1:** South Sudan population treated in 2006 by community directed treatment with ivermectin (CDTi) project areas [15]

CDTi project areas	Total population eligible for CDTi	Population treated (2006)	% Treated (2006) from annual CDTi target
Western Equatoria	425 752	247 653	58
Eastern Equatoria	1 508 733	151 475	10
Eastern Bahr el Ghazal	778 920	412 021	53
Western Bahr el Ghazal	505 933	70 460	14
Upper Nile	405 994	54 766	13
Total	3 625 332	936 375	26

In 2016, WHO estimated that about 7.5 million people in South Sudan required ivermectin prophylaxis [37]

In 1950, the entomologist DJ Lewis described the distribution of onchocerciasis and its vector *Simulium damnosum* (blackfly) in Western Equatoria and highlighted the high prevalence of onchocerciasis carrying blackflies in Mvolo County [16]. These findings are consistent with recent data from the South Sudan Ministry of Health Situational Analysis on Neglected Tropical Diseases and their control, and also with reports from the African Programme for Onchocerciasis Control (APOC) [14, 15]. Because onchocerciasis in the Western Equatoria region of South Sudan has not been controlled, the associated complications of onchocerciasis (NS and other forms of epilepsy) continue to be highly endemic in these areas.

Due to scarce funding, in 1972 Sudan stopped the use of insecticides to control the onchocerciasis vector in its southern region (now South Sudan) [13]. In 2006, as the Mundri area was considered co-endemic for loiasis (caused by the nematode worm *Loa loa* and spread by its vector, the deer and mango flies), ivermectin distribution was delayed by the South Sudan Onchocerciasis Task Force [15]. However, following training of ivermectin distributors on detection and management of severe adverse events, distribution was cautiously implemented in these areas [15]. Based on results of a large-scale survey conducted between 2002 and 2010, using the rapid assessment procedure for loiasis (RAPLOA), the areas of Mundri and Maridi were not marked for loiasis risk [17]. It is possible that deforestation in the Mundri and Maridi areas has led to the disappearance of loiasis.

### Ivermectin may reduce the incidence of NS/OAE

In the NS-affected areas of South Sudan (Western Equatoria) and northern Uganda (Kitgum, Pader and Lamwo), CDTi coverage was respectively low or not implemented at all in the past because of civil conflict. However, in northern Uganda, bi-annual mass distribution of ivermectin and larviciding of rivers infested by blackflies was introduced in 2012, and subsequently no new cases of NS have been reported since 2013 [18]. In contrast, in South Sudan where insecurity as a result of civil conflict continued to prevent the implementation of CDTi, new cases of NS/OAE continue to emerge [12].

Less ivermectin use before the onset of epilepsy was reported in persons with epilepsy compared to age matched controls during the same period in Democratic Republic of the Congo [19, 20]. Since CDTi, because few new children develop OAE, an age shift of NS/epilepsy cases towards older ages (20 years or above) has been observed [21, 22]. Moreover there is anecdotal evidence that ivermectin may reduce the frequency and severity of seizures [23].

Therefore we will carry out a population-based intervention to investigate if a CDTi programme is indeed able to reduce the incidence of NS/OAE in onchocerciasis-endemic areas in South Sudan. We hypothesise that in the Mundri and Maridi Counties of South Sudan, the implementation of bi-annual CDTi with a 100% geographical coverage and a minimum of 80% coverage of ivermectin eligible individuals will reduce the incidence of NS/OAE by at least half (50%). This assumption is based on findings from Uganda where no new cases of NS appeared after bi-annual administration of ivermectin and larviciding of rivers. In South Sudan larviciding of rivers will not be done, so the effect of ivermectin alone may not be as efficient. Moreover, other forms of epilepsy not related to onchocerciasis will not be preventable by ivermectin treatment.

## Methods and analysis

### Study setting

The study will be conducted in selected villages (where the population have not been displaced as a result of civil conflict) in Mundri and Maridi Counties in the Western Equatoria region of South Sudan (Fig. 2).

**Fig. 2 Fig2:**
[figure not shown]
Western Equatoria State Map showing the location of Mundri and Maridi

Mundri and Maridi have a high prevalence of NS and other forms of epilepsy [4, 12, 13]. The population of Mundri (East and West) and Maridi Counties are estimated at 82293 and 101 065 respectively [24]; farming is the main economic and livelihood activity. A small proportion of the population practise cattle herding and fishing. Water is mainly accessed from the Yei and Maridi Rivers, which are rapidly flowing and provide sufficient breeding sites for the *Simulium* vector (blackfly) that transmits *Onchocerca volvulus*. As a result of the recent civil conflicts in South Sudan, which also affected the study area, population movement in and out of the area has been high. However, most of the population did not leave the area but rather sought shelter in nearby villages that were considered safe [25]. This might also have been the case throughout the long period of the civil war that lasted for over 20 years before the peace agreement in 2005. The study will only include participants in villages that have lived in the area for at least 5 years.

## Study design

### Prevalence and incidence of NS and other forms of epilepsy

#### Population-based survey

In order to determine the prevalence and incidence of NS and other forms of epilepsy, a population-based household survey will be conducted prior to bi-annual CDTi.

The survey will start by short questionnaire-based interviews with village leaders and village health workers to capture village demographic information.

All individuals in the selected villages will be included in a door-to-door survey. A two-step epilepsy survey will be used to identify cases of NS and other forms of epilepsy. For screening, a pre-tested validated questionnaire for epilepsy consisting of five specific questions will be used [26].

The surveys will be planned when there are no major farming activities ongoing to obtain information on all people living in the village. If at the time of the home visit nobody is at home this household will be revisited later, at least once.

##### Training of interviewers

Research assistants living in the study area will be trained on how to conduct the screening process. Questionnaires will be translated into the local language and back translated into English to ensure no loss of meaning, and pilot tested.

##### Confirmation of cases

All suspected cases will be referred to a clinical officer trained to diagnose epilepsy or a medical doctor who will visit the suspected case at home and take a detailed medical history and perform a neurological examination. The clinical officer/medical doctor will confirm or reject the diagnosis of epilepsy.

##### Definitions

A *case of epilepsy* will be defined based on the International League Against Epilepsy (ILAE) as an individual with at least two unprovoked seizures with a minimum of 24 h separating the two episodes [27].

*Active epilepsy* will be defined as a person who is taking anti-epileptic treatment or who is not on anti-epileptic treatment but had at least one episode of seizures during the last 5 years.

A *new case of epilepsy* will be defined as a person who developed the first seizures within the last 24 months preceding the baseline survey (pre-CDTi incidence), or a person who developed the first seizures after the first round of CDTi and the second study visit to the household (post-CDTi incidence).

A *suspected NS case* will be defined as a person who presented with episodes of reduced consciousness with the head dropping forward repeatedly.

*OAE* will be defined as a person meeting the following six criteria: 1) Three years of living in an onchocerciasis-endemic region; 2) High prevalence of epilepsy in the village and families with more than one child with epilepsy; 3) History of at least two unprovoked epileptic seizures at least 24 h apart; 4) No obvious cause for the epilepsy; 5) Onset of epilepsy between the ages of three and 18 years; 6) Normal psychomotor development before the onset of epilepsy.

Epilepsy caused by perinatal trauma, head trauma, meningitis/encephalitis, and cerebral malaria can be suspected through medical history taking. Epilepsy caused by cysticercosis is difficult to differentiate from OAE but in the Maridi and Mundri areas there are no pigs, therefore neurocysticercosis does not exist in these areas. It is expected that the prevalence of epilepsy not caused by onchocerciasis will be < 1.4% (the median prevalence of epilepsy in Sub-Saharan Africa) [28].

#### Follow up of epilepsy cases

The person with epilepsy will be asked to come to the health centre to initiate anti-epileptic treatment. At the health centre, the person or caretaker will be counselled about epilepsy, and anti-epileptic treatment according to WHO epilepsy guidelines and the NS management guidelines proposed by R Idro [29] will be started.

#### Community-directed treatment with ivermectin (CDTi)

Following the initial household survey, CDTi will be implemented. The CDTi will be applied twice a year (6 months apart). The standard ivermectin dose of 150 μg/kg will be used [30]. Prior to implementation of the CDTi, the study team including community workers will meet with village and community leaders to explain the concept of CDTi. Community-directed distributers (CDDs) for the ivermectin will be trained to: (i) conduct a census; (ii) use measuring sticks to establish the number of ivermectin tablets to be given; (iii) detect and treat minor ivermectin side effects; (iv) refer cases of severe adverse events to the nearest health facility; (v) fill household treatment forms; (vi) keep an ivermectin inventory; and (vii) maintain CDTi distribution records and submit a report to the study coordinator. The Onchocerciasis Elimination Programme under the department of Preventive Chemotherapy, Neglected Tropical Diseases (PC-NTDs) in the Ministry of Health will coordinate the process. Ivermectin for the study will be supplied by the department of PC NTDs. Obtaining optimal CDTi coverage will be essential in order to be able to document an effect of the intervention. Therefore we plan to implement an epilepsy onchocerciasis awareness campaign in order to obtain > 90% CDTi coverage of eligible individuals. To reach this target we will get support from the state administration, and community involvement using the state radio, churches, mosques, community meetings and using the same research assistants to make house to house visits.

### Study inclusion criteria

All members of families who have lived for at least three years in the villages and are not planning to leave the village in the next two years.

### Exclusion criteria for ivermectin treatment

Children < five years old, pregnant women, women who have been lactating less than seven days, or very ill patients are ineligible.

### Sample size

We expect a crude incidence of new onset cases of NS/OAE in the Mundri/Maridi areas to be about 1.67% per year in all children aged five to 15 years [31]. With > 90% coverage of eligible individuals and 100% geographical coverage in the study area, we expect to decrease the incidence of NS/OAE in the five to 15-year-old population by 50%. Based on the reference proportion of 0.0150 (1.5% per year), alpha 5%, statistical power 80%, 2-sided testing, a total of 3475 children aged five to 15 years old need to be included in the study.

An adaptive study design will be used to ensure an adequately powered study. The NS/OAE incidence data will be cleaned after around 3000 children have been enrolled. The required sample size will be re-calculated using the actual observed incidence rate to ensure the study is adequately powered.

#### Epilepsy surveillance

A surveillance system for detecting new cases of epilepsy in the selected villages will be set up. The research assistants who carried out the baseline survey together with community-key informants will report suspected new epilepsy cases to a nurse supervisor, who in turn will verify the case history before referring to the study clinical officer/medical doctor for confirmation and initiation of treatment.

### Research study outcomes

The prevalence of NS and other forms of epilepsy in children and adults in selected villages in Mundri and Maridi counties in 2018.

Incidence of NS/OAE after implementation of bi-annual CDTi in these villages.

### Study procedures

Pre- and post-intervention household surveys will be performed using exactly the same methodology. The pre-intervention survey will be done within two months before the start of the bi-annual CDTi. A post-intervention survey will be done 2 years later.

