### Data analysis

The unit of analysis will be children between the ages of 5 to 15 years, who are most vulnerable for the development of NS/OAE. The incidence rate of NS/OAE at baseline will be calculated using incident cases in children 5 to 15 years of age during the preceding 24 months. This rate will be compared with the incidence rate of NS/OAE in the 24-month interval between the first and the second household surveys.

Data will also be collected on recent deaths that might be attributed to recent onset NS and other forms of epilepsy (household heads and community informants will be questioned). Deaths suspected to be because of NS/OAE will be considered as incident cases.

Descriptive statistics will be employed to present retention rates. Means and standard deviations will be presented for continuous outcome measures and frequencies and percentages will be presented for categorical variables. Chi-squared tests will be used to compare any group differences for categorical variables and *t*-tests will be used for continuous variables.

The incidence of NS/OAE pre- and post-intervention will be compared among those who received ivermectin twice a year over 2 years and those who missed at least one dose of ivermectin.

Conflict induced displacement of people during the study period is possible. In case of in or out migration only the data will be analysed of families who stayed for at least 5 years in the area.

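### Surveillance finds new cases only after baseline, and the post-CDTi count is not limited to survey-detected cases, so the two incidences may not be measured alike

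*Protocol article*

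**What the plan says.** On the surveys, Study procedures states: "Pre- and post-intervention household surveys will be performed using exactly the same methodology".

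On surveillance, the abstract's Methods places its start alongside treatment: "Bi-annual CDTi will be implemented in the villages and a surveillance system for epilepsy set up". Epilepsy surveillance adds: "A surveillance system for detecting new cases of epilepsy in the selected villages will be set up". It describes the route: "The research assistants who carried out the baseline survey together with community-key informants will report suspected new epilepsy cases to a nurse supervisor", who checks the history before a clinician confirms the case.

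On the comparison, Data analysis takes the earlier rate from a look back, counted in months: "The incidence rate of NS/OAE at baseline will be calculated using incident cases in children 5 to 15 years of age during the preceding 24". It then says: "This rate will be compared with the incidence rate of NS/OAE in the 24-month interval between the first and the second household surveys". Under Definitions, a new post-CDTi case is "a person who developed the first seizures after the first round of CDTi and the second study visit to the household (post-CDTi incidence"). Neither section says which source of detection a case must come from. Data analysis also counts deaths suspected to be due to NS/OAE, learned from household heads and community informants, and does not tie that inquiry to one period.

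On awareness, the CDTi section says: "we plan to implement an epilepsy onchocerciasis awareness campaign in order to obtain > 90% CDTi coverage of eligible individuals". The campaign includes house-to-house visits by the research assistants. Follow up of epilepsy cases offers anti-epileptic treatment to people who are identified.

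**The concern.** The trial's answer is a before/after contrast in the same villages. The Limitation section explains why there is no untreated comparison group. With no concurrent control, equal case finding in the two windows is what allows a change in incidence to be read as a treatment effect.

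The one stated safeguard, identical surveys, does not secure this. The quantity compared is incidence in two 24-month windows, and only the later window has people in the villages reporting cases as they arise. A child whose seizures begin after the first treatment round, and who is confirmed through surveillance but missed by the repeat survey, meets the post-CDTi definition as written. A similar child in the earlier window would have gone uncounted unless the baseline survey or the death inquiry found the case.

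If such cases are counted, the ratio mixes the effect of ivermectin with a change in case finding. A true reduction would look smaller, and with no true effect incidence would appear to rise.

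**Working it through.** **1. Sources of cases in each window**

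| | Pre-CDTi window | Post-CDTi window |
|---|---|---|
| Two-step door-to-door survey | yes, retrospective | yes, retrospective |
| Inquiry about deaths | yes (no period specified) | yes (no period specified) |
| Prospective surveillance | no | yes |
| Awareness campaign and treatment offer while cases arise | not described | yes |
| Numerator limited to survey cases | survey-based by construction | not stated |

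**2. Effect of unequal detection**

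The protocol gives no detection rates, so there is no stated figure to reproduce. The sensitivities below are assumptions.

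Observed ratio = true ratio × (post-CDTi sensitivity ÷ pre-CDTi sensitivity)

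The true ratio of 0.50 is the 50% reduction in the Sample size section.

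- 80% before, 95% after: 0.50 × 0.95/0.80 = 0.594, an apparent reduction of 41%.
- 70% before, 95% after: 0.50 × 0.95/0.70 = 0.679.
- 90% before, 95% after: 0.50 × 0.95/0.90 = 0.528.
- No true effect, 80% and 95%: 1.00 × 0.95/0.80 = 1.19.
- Equal detection, for example 80% in both: 0.50 × 0.80/0.80 = 0.50. Equal sensitivity cancels whatever its level.

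**3. What this could do to power**

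This step takes annual risks of 1.5% and 0.75%, a two-sided 5% test, full detection after CDTi, and the protocol's 3475 children as the number in each period. The last is an assumption: the protocol calls 3475 a total, and the usual two-proportion formula on its inputs gives 3104 per period, or 3365 with continuity correction. That discrepancy is a separate matter.

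Power = Φ{[(p₁ − p₂)√n − 1.96√(2p̄(1 − p̄))] ÷ √(p₁(1 − p₁) + p₂(1 − p₂))}, with p₁ = 0.015 × relative sensitivity, p₂ = 0.0075 and p̄ the mean of p₁ and p₂.

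| Pre/post relative sensitivity | Observed ratio | Power, annual risks | Power, 24-month risks (3.0% vs 1.5%) |
|---|---|---|---|
| 1.00 | 0.50 | 84% | 99% |
| 0.95 | 0.53 | 77% | 97% |
| 0.90 | 0.56 | 69% | 94% |
| 0.80 | 0.63 | 48% | 77% |
| 0.70 | 0.71 | 26% | 47% |

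**4. Effects in the other direction**

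- Study procedures allows up to two months between the baseline survey and the first treatment round, and Definitions starts the post-CDTi window at that round. If the second survey is 24 months after the first and cases are counted without person-time, the ratio is multiplied by 22/24 = 0.917: 0.50 × 0.917 = 0.46.
- Onset dates before baseline rest on recall over 24 months. If earlier onsets are pulled forward so that the pre-CDTi count is inflated by 10%, a 10% gain from surveillance is cancelled: 0.50 × 1.10/1.10 = 0.50. With 20% inflation it is reversed: 0.50 × 1.10/1.20 = 0.46. These percentages are also assumptions.

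**The case against.** The strongest reply is that nothing in the protocol says surveillance-only cases are counted. The Epilepsy surveillance section gives the system a clinical purpose, confirmation and treatment, and no analytic role. The abstract describes a repeated survey followed by a comparison, so counting survey cases alone is a natural reading. A condensed article may leave the data source to the full protocol or analysis plan. The possible gain is also limited. Surveillance adds only cases that both a whole-village repeat screen and the death inquiry would miss, and most confirmed children still living in the village should screen positive again. If there is migration, the analysis is confined to families who stayed at least 5 years, which removes many movers.

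Most of this stands as a limit on size and certainty. A reader might infer that the ratio is biased against ivermectin as a matter of fact. The documents do not support that: inclusion of surveillance-only cases is not stated, the sensitivities are unknown, and recall error or a shorter window could push the ratio the other way. A reader might also infer that every pre-CDTi case rests on one survey. That overlooks the death inquiry, which is a second source, although it cannot find living children whom the survey missed.

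The reply does not remove the point. The definition and the comparison are both written out in the article, and a surveillance-only case with onset in the window satisfies them. Nor can analysis alone settle it later: if the second survey's screeners work from the surveillance list, that survey's own sensitivity rises. That has to be decided before fieldwork.

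**Conclusion.** The concern holds in limited form. Case finding is asymmetric on the protocol's own text, and the promise of identical surveys does not extend to the two incidence windows. The sentence on identical methodology is not false but insufficient; the gap lies in Definitions, Epilepsy surveillance and Data analysis read together.

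For this mechanism alone the direction is clear: surveillance-only cases, if counted, dilute the observed reduction. With a post-CDTi sensitivity of 95% and a pre-CDTi sensitivity between 90% and 70%, a true ratio of 0.50 would be seen as 0.53 to 0.68. Those sensitivities are assumed, and the true gain may be smaller. The net direction across all sources of error is not established. Opposing errors of unknown size do not make the ratio interpretable, and this one can be removed cheaply, so the change should be made.

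**What to change.** In Definitions and Data analysis, base the primary comparison on cases found by the same two-step door-to-door screen at each survey, plus the same death inquiry in both periods. Count a surveillance-detected case only if the second survey's screen or the death inquiry also identifies it. State in Epilepsy surveillance that the second screen covers every household without use of the surveillance list. Report surveillance-only cases separately and add them in a sensitivity analysis.

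As a supportive check on changed reporting from the campaign and the treatment offer, compare pre- and post-CDTi incidence of new epilepsy that does not meet the OAE criteria. The Background section expects ivermectin not to prevent epilepsy unrelated to onchocerciasis. The check is imperfect: failing the OAE criteria, for example on age at onset, does not prove a case is unrelated to onchocerciasis, and the numbers will be small.

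The cost is wording and one extra tabulation, with no new data; surveillance and referral for care continue unchanged. The downside is that a few true cases leave the primary numerator. Independence from surveillance is also only partial, because the same research assistants may work on both and diagnosed families already know the diagnosis.
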